### Objectives

The overarching aim of the trial is to assess the clinical and cost-effectiveness of using eRATs for six cancer sites—colorectal, lung, bladder, kidney, oesophago-gastric and ovarian cancers—compared with usual care for patients in general practice. Our hypothesis is that provision of eRATs will expedite the diagnosis of symptomatic cancer resulting in better cancer outcomes.

The primary objective is to compare the effects of using eRATs (vs usual care) on the percentage of patients with a newly diagnosed cancer at one of the six sites whose cancer is staged as being stage 1 or 2 (vs stage 3 or 4).

A secondary objective is to investigate differences in the stage at diagnosis of a further six cancers without eRATs (combined): breast, melanoma, prostate, non-Hodgkin's lymphoma, larynx and uterus. This is to investigate the possibility of an effect whereby eRATs are associated with increased diagnostic activity beyond the eRAT cancers. We will also investigate differences in the number of patients diagnosed with the six eRAT cancers combined, and the total number of cancers (excluding non-melanoma skin cancer) diagnosed, use of the 2-week wait referral system (the main pathway for urgent investigation of possible cancer in England) or equivalent for the six eRAT cancers combined, and across all cancers; the routes to diagnosis for each of the six eRAT cancers,^18^ and for the six comparator non-eRAT cancers; the proportion of patients on a 2-week wait pathway receiving a diagnosis of cancer; whether a patient on a 2-week wait pathway has a diagnosis of cancer established (or refuted) within 28 days; 30-day and 1-year survival for those with cancer; the rate of cancer investigations—namely colonoscopies, sigmoidoscopies, upper gastro-intestinal endoscopies, chest X-ray examinations, abdominal ultrasound scans and abdominal CT scans. We will also conduct parallel cost-effectiveness analyses, service delivery modelling and a process evaluation.

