#### Secondary outcomes

A range of secondary outcomes will be examined:

The binary stage at diagnosis of a further six cancers without eRATs will be identified from NCRAS, and compared between intervention and control practices. This is to investigate the possibility of a ‘spillover’ effect whereby eRATs are associated with increased diagnostic activity beyond the eRAT cancers.The practice’s number of patients diagnosed with the six eRAT cancers combined, and the total number of cancer cases, from NCRAS.The number of patients investigated or referred under the 2-week wait system for the six eRAT cancers combined, and in total, from Cancer Waiting Times data.Route to diagnosis from the Routes to Diagnosis Dataset,^18^ which uses Hospital Episode Statistics data. This will be categorised into four possible routes: emergency attendance, 2-week wait referral, GP referral and ‘other’. We will collect this information for each of the six eRAT cancers, and for the six comparator non-eRAT cancers.The 2-week wait performance measures, from Cancer Waiting Times data, for the six eRAT cancers combined, and for all cancer referrals:Whether a patient on a 2-week wait pathway received a diagnosis of cancer. When aggregated, for example at the practice level, and expressed as the proportion of patients who received a cancer diagnosis, this is known as the conversion rate.The duration between 2-week wait referral and diagnosis of cancer in days.Whether patients referred on a 2-week wait referral and who received a cancer diagnosis were diagnosed within 28 days, the Faster Diagnosis Standard (introduced in 2022).Detection rate—the proportion of a practice’s cancers which are identified via the 2-week wait pathway.Survival measures (from date of diagnosis): 30-day; 1-year (identified from NCRAS). 5-year survival will also be reported, but the main trial will report at 30 days and 1 year, with 5-year data being a subsidiary report. These outcomes will use all-cause mortality data from the Office for National Statistics.Adverse events (using data from the Diagnostic Imaging Dataset): these are expected to be few, and largely related to complications from hospital investigation, such as colonoscopy. There is no mechanism for adverse events to be collected using routine data. We will, however, estimate any change in the expected number of adverse events from imaging investigations (colonoscopies, sigmoidoscopies, upper gastro-intestinal endoscopies, chest X-ray examinations, abdominal ultrasound scans and abdominal CT scans) through investigating any change in the rate of these investigations in intervention practices relative to control practices (see data analysis section). Potential adverse psychological consequences of being labelled with ‘possible cancer’ will be further explored in the process evaluation.

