For rate outcomes (number of 2-week wait referrals, cancers and imaging investigations), we will analyse the rates per 100 000 registered patients per year by age–sex strata using mixed-effects Poisson regression models including a random intercept for practice. These models will include trial arm as a predictor and will adjust for the age and sex of the strata, and at the practice level for the minimisation variable (2-week wait referral ratio) and deprivation (quintile of IMD overall score). The models will be further adjusted at the practice level for list size, clinical IT system used, Care Quality Commission overall rating, and for the age and sex case mix of practices should these covariates be found to be associated with the outcome (even if not unbalanced with respect to allocation). Case mix will be incorporated by including variables for counts of practice populations in different age–sex strata (5-year age groups by sex, excluding one age–sex stratum that can be determined once all others are known).

All the above analyses will combine data for the six eRAT cancers for each model. For outcomes related to 2-week wait referrals, data will be combined for all referral pathways relevant to the six eRAT cancers. To investigate whether the eRATs produce a spillover effect, whereby diagnostic activity is increased for other cancers, we will repeat all analyses using data for the six non-eRAT cancers combined for each model. Investigation of a spillover effect for 2-week wait referral outcomes will use data for all referral pathways combined.

Additional sensitivity analyses will be conducted for the primary outcome in order to explore moderation arising from practice-level characteristics, using interaction terms. Although the trial has not been powered to detect low-to-moderate subgroup differences, such as differences in a single cancer site, large interaction effects that differ with respect to the direction of effect across subgroups are of interest. The potential impact of missing staging data on the primary outcome will also be explored through use of multiple imputation methods making use of auxiliary variables, such as survival time, morphology and grade, to improve the missing at random assumption in line with previous work).^37^

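### For the 2-week wait outcomes, spillover is tested on a total that contains the eRAT pathways, so direct effect and spillover cannot be told apart

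*Protocol article*

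**What the plan says.** The relevant text is in Data analysis, in the paragraph on which cancers and pathways enter each model.

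- Purpose of the spillover analyses: "To investigate whether the eRATs produce a spillover effect, whereby diagnostic activity is increased for other cancers".
- Data for the main 2-week wait analyses: "data will be combined for all referral pathways relevant to the six eRAT cancers".
- Data for spillover in general: "we will repeat all analyses using data for the six non-eRAT cancers combined for each model".
- Data for spillover in the 2-week wait outcomes: "Investigation of a spillover effect for 2-week wait referral outcomes will use data for all referral pathways combined".

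Two other sections confirm that the wider set is a total. Secondary outcomes lists the referral count as "The number of patients investigated or referred under the 2-week wait system for the six eRAT cancers combined, and in total", and the 2-week wait performance measures "for the six eRAT cancers combined, and for all cancer referrals". Objectives describes 2-week wait use "or equivalent for the six eRAT cancers combined, and across all cancers".

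On model terms, the rate models are described thus: "These models will include trial arm as a predictor and will adjust for the age and sex of the strata", followed by practice-level covariates. The binary 2-week wait models adjust for referral type and the waiting-time models for referral pathway. No interaction of either with trial arm is stated.

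Stage at diagnosis is handled differently. That model pools all twelve cancers, adds an indicator for whether the site has an eRAT, and includes its interaction with trial arm.

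**The concern.** The question is about other cancers, but the data set chosen to answer it contains the referrals the intervention is designed to change. One arm effect is estimated across both groups of pathways, so it is a blend of direct effect and spillover. The outcomes concerned are the referral rate, conversion, diagnosis within 28 days and waiting time.

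Two errors become possible. A purely direct effect moves the estimate labelled spillover away from 1. Conversely, a fall in referrals on other pathways can be cancelled by a rise on the eRAT pathways and go unseen. Whether eRATs raise activity beyond their own cancers is a stated secondary interest of the trial, and the first error is most likely precisely when the tool works as intended.

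**Working it through.** The plan states no figure for this analysis, so there is nothing to reproduce. The check compares the data sets and then shows how far a direct effect carries over.

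**Step 1: which data enter which analysis**

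| Outcome | Direct effect | Spillover | Separation |
|---|---|---|---|
| Stage | six eRAT cancers | all twelve cancers | eRAT indicator × arm |
| Routes, survival, cancer counts | six eRAT cancers | six non-eRAT cancers | separate data sets |
| 2-week wait outcomes | eRAT-relevant pathways | all pathways | none stated |

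Only in the last row does the spillover data set contain the direct-effect data with nothing to tell them apart. Adjusting for referral type or pathway does not help: a main effect still leaves one common arm effect over both groups.

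**Step 2: expected rate ratio**

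Let s be the eRAT-relevant share of control-arm referrals, RR_direct the arm effect on those pathways and RR_other the effect on the rest. Then

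RR_all = s × RR_direct + (1 − s) × RR_other.

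With no spillover, RR_other = 1 and RR_all = 1 + s(RR_direct − 1).

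The document gives neither s nor RR_direct; both are assumed below. Justification of cancer sites puts the six sites at about half of incident cancers, but that is a share of cancers, not of referrals.

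| s | RR_direct 1.1 | 1.2 | 1.3 |
|---|---|---|---|
| 0.3 | 1.03 | 1.06 | 1.09 |
| 0.5 | 1.05 | 1.10 | 1.15 |
| 0.6 | 1.06 | 1.12 | 1.18 |

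Every departure from 1 in this table is direct effect.

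**Step 3: masking**

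With s = 0.5, RR_direct = 1.2 and RR_other = 0.8, RR_all = 0.5 × 1.2 + 0.5 × 0.8 = 1.00. A 20% fall on the other pathways would not show.

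**Step 4: chance of a significant result when there is no spillover (illustration)**

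Inputs: 239 practices per arm and α = 0.05 from Sample size (α taken as two-sided), and an assumed between-practice coefficient of variation k. The standard error of the log rate ratio is k × √(2/239).

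- k = 0.3: SE = 0.0274. For s = 0.5 and RR_direct = 1.2, log(1.10)/0.0274 ≈ 3.47, giving a probability of about 94%. For s = 0.3 and RR_direct = 1.1 it is 19%.
- k = 0.4: the same two settings give 74% and 13%.

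A simulation at k = 0.3 (2,000 runs per setting, gamma-Poisson counts, an assumed 600 referrals per practice) agreed within about 5 percentage points. When the analysis was restricted to the other pathways, rejection was 4% to 6%, which is the nominal level.

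**The case against.** **The paired result is available.** The plan analyses eRAT-relevant pathways as well as the total. A reader who saw 1.20 and 1.10 side by side, and knew s = 0.5, could work back to RR_other = (1.10 − 0.5 × 1.20)/0.5 = 1.00. This stands in part. It is why one should not infer that the trial would inevitably announce a false spillover effect. But the plan specifies no such contrast, and subtracting two overlapping estimates by hand gives no confidence interval.

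**Pathways may not match cancer sites.** The article speaks of pathways relevant to the eRAT cancers and treats pathway and site as different things. If a pathway serves both an eRAT cancer and a comparator cancer, excluding it would lose any spillover there. This is a fair limit on the remedy and could explain the choice made. It does not turn the total into a test of spillover.

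**Spillover is tested properly elsewhere.** This stands. The stage model separates the effects by interaction, and the other repeats use the six non-eRAT cancers. It would be wrong to infer that spillover in general is mishandled, or that all other outcomes simply exclude the eRAT cancers: the stage model includes them and separates them.

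**The wording might mean all other pathways.** The documents do not support this. The same paragraph restricts the pathways explicitly when a restriction is meant, and Objectives and Secondary outcomes both describe a total.

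**Conclusion.** The point holds for the secondary 2-week wait outcomes. As written, the analysis labelled spillover estimates the overall effect on 2-week wait activity. Whenever there is a direct effect and no spillover, its expected rate ratio differs from 1, by an amount diluted by the eRAT share: 1.03 to 1.18 over the assumed range (s of 0.3 to 0.6, RR_direct of 1.1 to 1.3). The existence of this carry-over does not depend on those values; its size does. The significance probabilities also rest on an assumed between-practice variation and are illustrative only. No size was computed for conversion, 28-day diagnosis or waiting time, where the same overlap applies.

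A reader might infer that a false claim of spillover is certain, or that the main result is compromised. Neither follows. With a small direct effect and a small eRAT share, the chance of a significant result is only 13% to 19% in the illustration, and the eRAT-pathway result will be available for comparison. The primary outcome, the sample size, the stage spillover model and the repeats on the six non-eRAT cancers are untouched. The all-pathway total also remains a valid outcome in its own right; what is wrong is its use as the spillover test.

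**What to change.** In Data analysis, replace the sentence on spillover in the 2-week wait outcomes with a model of the kind already specified for stage: fit each 2-week wait model on all pathways, add an indicator for eRAT-relevant versus other pathway group and its interaction with trial arm, and report the arm effect in the other group, with its 95% CI, as the spillover estimate. A simpler alternative is to restrict the spillover analysis to pathways not relevant to the six eRAT cancers. Report the all-pathway result only as overall 2-week wait use, the total already listed under Secondary outcomes.

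The cost is small. No new data are needed, because the plan already has to identify the eRAT-relevant pathways, and the other group is what remains. The real work is a classification list fixed before analysis. A pathway serving both eRAT and comparator cancers should be classed as eRAT-relevant, and the report should state that spillover within such shared pathways is then not captured.

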### Data management

Cancer registry data (NCRAS) will be managed and prepared by the registry themselves and securely, electronically transferred to the study team. There will be no patient identifiable data within these datasets. Data from NCRAS will be stored on the secure data resource hub at the University of Exeter (which meets requirements for secure storage of sensitive data) and linked to existing practice data held within ExeCTU’s REDCap database. The data will be stored and retained in accordance with registry policies.

The nested studies rely on identifying patients from in-practice usage reports. These reports contain depersonalised (pseudo-anonymised) data. The practice will send a copy to the trial team with the original practice ID number removed. The local in-practice reports will be securely and electronically transferred to a secure Exeter CTU computer.

In the recruitment of patients (and NHS staff) for interviews, questionnaires or permission for access to medical notes, participant details will be passed securely between NHS services and the research team. All participants agreeing to interview, to complete a questionnaire and/or medical notes review, and all GPs agreeing to interview will be allocated a unique study ID, and the information linking their ID to their personal details will be kept securely at the University of Exeter. All other participant-related paper records will be anonymised and stored separately from the personal information. The electronic database for the trial will be stored on the secure servers of the University of Exeter with password-controlled access provided for the research team by ExeCTU. Single data entry with extensive in-built validity checks will be used to reduce the risk of transcription errors.

Audio recordings will be digitised, encrypted and stored on the university’s secure server. Audio recordings will be retained until after anonymised transcripts have been finalised and analysed. At this stage they will be securely and permanently deleted. Access to personal data will be restricted to the research team. Names and participant details will not be passed to any third parties and no named individuals will be included in the outputs. All participants (patients, NHS staff) will be asked for their consent for the study team to retain interview transcripts for the purposes of future research by those involved directly in the study team or to be used for educational purposes.

Informatica Systems Ltd has developed a separate agreement (‘Data processing deed’) for intervention practices, which will be used between the GP practices and Informatica Systems Ltd. The deed was necessary because the development of Skyline has affected the processing arrangements for the eRATs software that is used. The ERICA research study will still use the organisation information document which outlines the research team’s data processing requirements, to be signed between the practice and sponsor.

All study data will be kept for 10 years (unless data registry policy requires otherwise) under secure conditions on University of Exeter secure servers. Data will also be subject to standard secure storage and usage policies.

#### Trial steering committee (with data monitoring committee responsibilities)

The responsibilities of the trial steering committee (TSC) will be to review the main study protocol and any amendments, monitor and supervise the trial towards its interim and overall objectives, review relevant information from other sources and help to resolve problems brought by the trial management group (TMG). The TSC will therefore provide overall independent supervision for ERICA on behalf of the funders and the sponsor. Meetings will be held at regular intervals determined by need and not less than twice a year. Routine business will be conducted by telephone, videoconference, and email. The TSC will also operate as a data monitoring committee with responsibility for the overall conduct of the trial. There will be a time lag between practices ‘entering the trial’ and data availability from cancer registries. The time lag will be such that data will be available only when practices have completed data collection. Therefore, interim analyses to assess whether the trial was effective, and to support a decision whether to stop the trial early, would be unnecessary as data collection (and practice participation) would have already ceased.

#### Trial management group

A TMG has been established and includes those responsible for the day-to-day management of the trial and those supporting the delivery of the trial and associated stakeholders, including representatives of the local clinical research networks and Macmillan. The group will monitor all aspects of the conduct and progress of the trial, ensure that the protocol is adhered to and take appropriate action to safeguard participants and the quality of the trial itself. The group will meet regularly (monthly in the first instance, until recruitment has completed) in person and/or by phone or over the internet (via Microsoft Teams).

#### Core study team

The core study team (chief investigator, trial manager (TM)) will meet weekly during the study. Day-to-day running of the trial will be the responsibility of the TM. The TM will have access to the ExeCTU suite of standard operating procedures (SOPs) and will ensure that the trial is run in compliance with all relevant SOPs (eg, assessment, processes and reporting, data management, study staff health and safety).

### Nested studies

#### Health economics

We will estimate the cost and cost-effectiveness of the eRATs versus usual diagnostic practice using the primary perspective of the NHS and personal social services (ie, third-party payer). We will estimate the cost-effectiveness of the intervention based on the primary outcome and secondary survival outcomes (30 day and 1 year; 5-year survival will be a subsidiary report) for the six cancer sites with eRATs and report the results using the latest guidelines.^39^ For colorectal, lung and ovarian cancers we will use decision analytic models to combine data from the within-trial analysis of ERICA intervention on costs and benefits, with longer estimates derived from the evidence synthesis of the costs and benefits of stage of diagnosis and disease progression to estimate the cost per quality-adjusted life-year over the longer term.^40^ For fuller details see online supplemental appendix C.

#### Service delivery modelling

This will investigate the key factors central to the (re) organisation of NHS diagnostic services for cancer referrals. We will use a range of methods, both quantitative and qualitative, to analyse service delivery alternatives. Specifically, we will aim to use modelling approaches to explore the likely implications of different scenarios across dimensions of performance, outcomes and costs. Fuller details are in online supplemental appendix D.

#### Process evaluation

The process evaluation work aims to identify and investigate the contextual factors that impact on the effectiveness of the eRATs, with particular focus on intervention fidelity and GP engagement. The impact of the eRATs on the patients’ experience of their GP consultation and their experiences of subsequent care will also be explored. Fuller details are in online supplemental appendix E.

#### GP workload

This nested study aims to explore, in terms of consultation time, the impact of the use of eRATs by GPs on their workload, and patient ‘flow’ through consulting sessions. It will also explore workload in the week following the index consultation in which an eRAT was activated. Fuller details are in online supplemental appendix F.

### Patient and public involvement and engagement

Our patient and public involvement and engagement (PPIE) group, including cancer survivors, has been consulted widely during the development of this study. The PPIE group has reviewed and commented on the protocol and supported the development of all patient-facing materials, including information sheets and study lay summaries. One experienced PPIE representative sits on the TMG and another is on the TSC. A total of seven people have joined our PPIE group for this study and will contribute by reviewing study materials and documentation, commenting on and proof reading reports and contributing to dissemination activities. This group will be supported in their work by the South West Peninsula applied research collaboration PPIE team—for example, by attending workshops on critical appraisal skills. All PPIE representatives will be recompensed for their time given to the study.

